### Blinding

Both patients and investigators will be blinded to the assigned group. To achieve the blind method, the blind codes of this study which consist of two levels, will be held by the sponsor. The level I blind code will designate whether each drug number will be associated with drug A or drug B, respectively; the level II blind code will designate whether drug A and drug B will be a trial drug or a placebo. According to the statistical analysis plan, the level I blind code will not be revealed until the statistical analysis, which will be carried out by a statistical analyst. After the analyst writes a report, we will hold a concluding meeting, the level II blind code will be revealed for the first time on the spot, and the unblinded staff will sign on the blind code.

Unblinding will be permissible when serious adverse events occur and the actions to protect the safety of the subject must be taken immediately during the study. When urgent unblinding is required, the treating physician shall report to the principal investigator of the site. After approval, the emergency letter sent with the drug will be unpacked, the type of drug administered will be identified, a prompt rescue will be made, and the potential reasons will be clearly explained; the medical record will be signed and dated. Concurrently, the subject will be discontinued from the trial.

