## Methods and analysis

### Trial design

This multicenter, randomized, patient- and investigator-blinded, placebo-controlled, parallel-group study will be conducted at 18 hospitals in China and Australia. Patients fulfilling the Rome IV FD-PDS criteria [17] will be recruited primarily through advertisements on hospital websites and outpatient clinics. Before randomization, all patients will be required to provide written informed consent. In response to the COVID-19 pandemic, face-to-face site visits may be replaced by telephone consultations, and study materials may be distributed and returned via mail. The study protocol (version XYYY-V-2.1) has been approved by ethics committees at all participating hospitals following the Declaration of Helsinki and is reported based on SPIRIT (Supplementary file 1) [18]. This trial has been registered on ClinicalTrials.gov (NCT03825692). A flow diagram of the trial is shown in Fig. 1.

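### Emergency unblinding is allowed when action must be immediate, yet the site principal investigator's approval is placed before the letter is opened

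*Protocol article*

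**What the plan says.** Emergency unblinding is dealt with in the second paragraph of the Blinding section of the protocol article. The trigger is stated first: "Unblinding will be permissible when serious adverse events occur and the actions to protect the safety of the subject must be taken immediately". For such urgent cases the procedure is that "the treating physician shall report to the principal investigator of the site. After approval, the emergency letter sent with the drug will be unpacked". That sentence then lists, in this order, identification of the drug, the rescue, an explanation of the reasons and a signed, dated medical record. The paragraph ends: "Concurrently, the subject will be discontinued from the trial".

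The only other mention of unblinding during the trial is in Withdrawal and dropout criteria, where an unblinded case is listed as a ground for withdrawal by the investigator. That item says nothing about how the code is opened.

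**The concern.** An emergency code break exists so that the person treating the patient can learn the allocation at once when that knowledge bears on care. Here the trigger is already restricted to cases in which "the actions to protect the safety of the subject must be taken immediately during the study". The procedure attached to that trigger nevertheless starts with a report to another person and makes the opening of the letter follow that person's approval. The text describes no less urgent class of unblinding for which prior approval would be the natural safeguard, so the approval step falls entirely on the urgent cases.

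What is at stake is timely access to the code for a patient with a serious adverse event, and an instruction that site staff can follow without having to choose between its two halves.

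**Working it through.** No arithmetic applies. The article states no figure on this point, and the question is the order of steps. The check was to set the sentences side by side and then look through the rest of the article for anything that relaxes them.

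**1. Trigger.** Two conditions are joined: a serious adverse event has occurred, and action to protect the subject is needed at once. No other trigger for unblinding an individual patient during the trial is given.

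**2. Order of steps once the trigger is met.**

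- The treating physician reports to the site principal investigator.
- Approval is given. The text does not name the approver, but the preceding sentence makes the site principal investigator the natural reading.
- The emergency letter is opened.
- The drug is identified.
- The rescue is made.
- The reasons are explained, and the record is signed and dated.
- At the same time, the subject is discontinued.

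**3. Status of the approval step.** The report is worded as mandatory, and the opening of the letter is placed after approval. The word *only* (the letter may be opened only after approval) is an inference. It follows because no other way to the letter is described.

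**4. Search for an exception.**

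- Blinding: the two-level blind codes are held by the sponsor and revealed for the analysis and at the concluding meeting. No emergency use of them is described.
- Withdrawal and dropout criteria: unblinding appears only as a ground for withdrawal.
- Safety observation: reporting and causality review of adverse events, with nothing on opening the code.
- Data management: the monitoring board's remit, with nothing on opening the code for an individual patient.

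None of these lets the treating physician open the letter before approval.

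**5. Result.** The condition in step 1 is immediacy. The sequence in step 2 puts another person's permission between that condition and the code, and it lists the rescue after both approval and identification. As written, the procedure can delay access to the code in the situation that justifies it. Whether it would do so in a given case, and for how long, cannot be derived from the article.

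**The case against.** The best reply is that the sentences do not strictly contradict each other. Immediacy is required of the protective action, not of opening the letter. The implied approver is at the site, the letter travels with the drug, and a quick local approval is compatible with urgency. This stands in part: the defect is a tension that can cause delay, not a logical impossibility. It does not remove the point, because the approval step is stated as part of the procedure, has no exception, and applies to urgent cases alone.

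Several stronger readings are tempting, and the document does not support them.

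- **That the physician must wait before treating.** A reader might infer this from the place of the rescue in the sequence. The paragraph governs the code break, however, and does not expressly forbid care before approval. Withdrawal and dropout criteria also let the investigator withdraw a subject after an adverse event with no approval step stated. What remains is that the order of the wording invites the misreading.
- **That a deputy or an out-of-hours route is missing.** A condensed article commonly leaves such detail to the full protocol, so its absence is no finding. The approval step is different, because the article states it.
- **That mailing of supplies sends the code to the patient's home or leaves the physician without it.** Trial design says that "study materials may be distributed and returned via mail" in response to the pandemic, but it does not mention emergency letters. The Implementation plan has coded drug distributed to the sites, so the letter may well go no further than the site.
- **That the blind for the patient-rated primary endpoint is damaged.** The record of a code break must be signed and dated, and the subject is discontinued at the same time. Undocumented code breaks would require staff to depart from the protocol, which cannot be assumed.

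**Conclusion.** The point holds in a narrow form. The article states an approval step that sits badly with its own urgency condition, and the sentences must be reconciled. This is a fault in a stated rule, not a gap left by condensation: the full protocol may add contact details or delegates, but the published order would still put approval first.

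The size cannot be estimated. The article gives no serious adverse event rate and no approval time. The rule covers 480 planned patients at 18 hospitals over 8 weeks of treatment, but these figures describe its reach and do not measure harm. Emergency code breaks are probably few, and approval may often be quick. There is no effect on sample size, alpha, power or the primary analysis.

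Two assumptions are made: that the approver is the site principal investigator, and that no exception to the stated order exists in a document not shown here. The correction is still worth making, because each affected case is urgent by definition and the change is cheap.

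**What to change.** Reconcile the sentences of the emergency paragraph in the Blinding section so that two things are clear: the approval step cannot delay emergency access to the code, and rescue is not worded as depending on approval. One possible wording has the code break documented and reported to the site principal investigator when the letter is opened. This is a matter of access to the code. It sets no treatment, and all treatment decisions remain with the physician.

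The trigger condition and the signed, dated record can stay as they are. The change needs revised wording and an instruction to sites. Trial status describes recruitment as continuing, and Plans for protocol amendments already provides the route. Randomization, sample size and analysis are untouched. The downside is a slightly higher chance of an unnecessary code break, which the unchanged trigger and the required record limit.

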### Interventions

The intervention will have a total duration of 8 weeks. Eligible patients will be randomly assigned to receive either the trial drug or a placebo. Their medication will be free for the entire study period.

#### Experimental

ZZKZ (0.43 g per capsule) (Lonch Group Shuangren Pharmaceutical Co., Ltd.; batch number: Z20020003) is composed of the following TCM crude drugs: Rhizoma Atractylodis Macrocephalae (0.16 g, accounting for 37.5%), Fructus Aurantii Immaturus (0.11 g, accounting for 25%), Radix Bupleuri (0.08 g, accounting for 18.75%), and Fructus Crataegi (0.08 g, accounting for 18.75%). The parts of the plant used are listed in Chinese Pharmacopoeia (version 2015). ZZKZ is a standardized product that uses the four dry herbs manufactured as concentrated granules (using 65% ethanol as solvent) and packed into capsules. The ratio of herbal drugs to extract is 2.79:1. The manufacturer keeps the lot numbers of the raw materials with the authentication of raw materials. Qualitative tests, including chromatographic analysis, microscopic identification, thin-layer identification, examinations of moisture, impurities, total ash, heavy metals, harmful elements, and residual sulfur dioxide, have been carried out for ZZKZ, the four herbs by the manufacturer.

#### Placebo

ZZKZ mimics (0.43 g per capsule) (Lonch Group Shuangren Pharmaceutical Co., Ltd.). The placebo does not contain any drug, and starch and microcrystalline cellulose are used as filling agents. The placebo for ZZKZ capsules (0.43 g) contains starch and microcrystalline cellulose in a ratio of 2:1, with an additional amount of an appropriate amount of a food-grade pigment solution, using magnesium stearate as a lubricant (0.5%). Food additives that meet China’s quality standards for pharmaceutical excipients are used for placebo color modulation. The placebo has the same taste, odor, and color as ZZKZ. The dose, method of use, and duration of the investigational products are listed in Table 1.

**Table 1 Tab1:** Dose and duration of the investigational products

Group	Investigational product	Dose and methods	Duration (weeks)
ZZKZ	ZZKZ	3 capsules at a time, 3 times a day, taken orally 10–15 min before meals	8
Placebo	ZZKZ Mimics	3 capsules at a time, 3 times a day, taken orally 10–15 min before meals	8

### Concomitant drug

Long-term concomitant medication which may have treatment effects on PDS should be avoided:Medicines related to the treatment of PDS should not be administered during the study.Patients taking non-steroidal anti-inflammatory drugs such as aspirin before enrollment may continue taking these drugs without increasing or reducing the dose.Opioid preparations will be prohibited during the trial. If used before enrollment, sedative and hypnotic drugs (e.g., patients with insomnia take diazepam, etc., as needed) and antidepressants can be continued without increasing or decreasing the dose.Some antibiotics that affect gastric motility will be prohibited during the trial: macrolide antimicrobial or azole antifungal.During the trial, acupuncture, massage, cupping, and other TCM therapies related to the treatment of this disease shall not be used.If the participant is eligible by the inclusion criteria but needs to continue taking medicine or to add other drugs or treatment methods for the consideration of comorbid illness or changes of illness state, it will be necessary to record all information to the case report form, including the name of the drug (or other therapies), the dosage, use frequency, and time.

### Outcomes

#### Primary outcome

Participants self-rate on the VAS for the degree of discomfort with both symptoms of postprandial fullness and early satiation, degree of discomfort will be indicated by a 10-cm line marked from 0 (asymptomatic or no discomfort) to 10 (extreme severe or extreme discomfort) [19]. The rating will be made once a day and 7 days a week via a diary card. For VAS scores for postprandial fullness discomfort and early satiety, the integral average for both symptoms over the past week will be evaluated, and a 50% decrease from baseline in the integral average at 8 weeks will be recorded as a response. The proportion of the response at 8 weeks after randomization will be considered the primary efficacy endpoint.

#### Secondary outcomes

##### VAS score of each FD symptom

On the diary cards, subjects will be recorded the VAS of each FD symptom daily, including abdominal distension (mid-epigastric distension or lower abdominal distension), abdominal pain (mid-epigastric pain or lower abdominal pain), epigastric burning sensation, nausea, excessive eructation, heartburn, vomiting, regurgitation, dysphagia, abdominal enlargement, and defecation smoothness [20]. VAS will be scored on a scale of 0–10 which the higher the score, the more severe the sign. The record will be made once a day and 7 days a week. The investigators will use the average VAS scores as the symptom intensity score for the week. The change in each symptom’s score at 8 weeks after randomization relative to the baseline will be evaluated.

##### Overall treatment response rate

The overall treatment efficacy will be evaluated using a 7-point Likert Overall Evaluation Scale [21]. The clinical investigators will ask the subjects the following question weekly: “In the last week, how much have your dyspeptic symptoms been alleviated as compared to pre-treatment?” There will be seven options: (1) the symptoms improved significantly, (2) the symptoms improved, (3) the symptoms improved slightly, (4) the symptoms did not change, (5) the symptoms aggravated somewhat, (6) the symptoms aggravated, and (7) the symptoms aggravated significantly. At the last visit time point of the treatment cycle, patients who selected (1) and (2) will be defined as treatment responders, and those who chose (3) to (7) will be defined as non-responders. The response rates at 8 weeks after randomization between the groups will be compared for differences.

##### Short Form Nepean Dyspepsia Index (SFNDI)

SFNDI is a reliable and valid measure of FD’s quality of life. It has ten items on how subjects’ stomach pain, discomfort, or other epigastric symptoms affected their lives over the last 14 days [21]. Add up the ten items for each of the five subscale scores (range of each subscale 2–10). The SFNDI score changes at 4 and 8 weeks after randomization relative to the baseline will be calculated.

##### Hospital Anxiety and Depression Scale (HAD) score

HAD, mainly used in patients in general hospitals, provides two sets of tests to assess anxiety and depression [22]. Among them, “A” stands for anxiety items, “D” stands for depression items, and each item is scored at four levels. Each of the two sets of items is superimposed to obtain their respective total score. A total score of 0 to 7 indicates normal, 8 to 10 indicates borderline abnormal, and 11 to 21 indicates abnormal. The HAD score changes at 4 weeks and 8 weeks after randomization relative to the baseline will be calculated.

### Safety observation

Vital signs: Body temperature, heart rate, blood pressure, and respiration (once at each follow-up visit)Blood routine (RBC, WBC, HGB, PLT, PMN%, and LYM%), urine routine (urine WBC, urine RBC, urine PRO, and urine GLU), stool routine plus fecal occult blood test (FOBT, WBC, and RBC), all this will be tested once before and after treatment respectively, twice in total.Hepatic function (alanine aminotransferase (ALT), aspartate aminotransferase (AST), total bilirubin (TBil), alkaline phosphatase (ALP), and gamma-glutamyl transferase (GGT)) and renal function (serum creatinine (SCr), and blood urea nitrogen (BUN)) will be tested once before and after treatment, twice in total.Electrocardiogram (once before and after treatment, respectively, twice in total)Severity and incidence of adverse events (recorded in detail at any time)

During the trial, each participant will receive safety monitoring. Potential adverse effects will be identified from the data collected by the post-marketing adverse drug reaction monitoring center and the safety data from preliminary trials [23]. All adverse events will be reported to the ethics committee and office of the clinical trial institution. They will review all documented harms during the trial and judge with regard to causality. The enrollment, interventions, and assessment schedule are summarized in Fig. 2.

**Fig. 2 Fig2:**
[figure not shown]
Schedule of the trial

### Data management

There will be two ways for patients to record their diary cards, using either paper diary cards or an electronic diary (eDiary). Both paper diary cards and eDiary will record the severity of patients’ symptoms related to FD, including postprandial fullness discomfort, early satiety, abdominal distension (mid-epigastric distension or lower abdominal distension), abdominal pain (mid-epigastric pain or lower abdominal pain), epigastric burning sensation, nausea, excessive eructation, heartburn, vomiting, regurgitation, dysphagia, abdominal enlargement, and defecation smoothness. All the investigators will receive training regarding data management and participants’ education for instructions on using the paper diary cards and/or eDiary. For eDiary, in order to ensure that participants can fill out the diary card every day, the system will send a text message to the participants who have not filled out the diary card every night for a reminder. Also, researchers will be able to use the system to check whether participants have filled out the diary card. The original medical records will be kept intact by the site investigators as original documents. The data will be inputted into the eCRF which the database has been established before recruitment. Investigators will be responsible for verifying the accuracy of the data. Data locking will be completed by the data management team, researchers would not be able to modify the data after locked. All research data, including paper and electronic documents, will be kept for at least 5 years after publication. All participant data collected during the trial will be deidentified and available for anyone who wishes to access the data immediately following publication.

A Data and Safety Monitoring Board (DSMB) is set up to review the protocol and the research data. The DSMB members will meet regularly to review the trial data according to ethical and safety standards and monitor the data’s authenticity and completeness based on the study design. The DSMB will also review the trial progress, determine adverse events, and have the authority to decide whether the study will need to end early.

### Quality control and assurance

This trial protocol has been reviewed and revised by experts in gastroenterology, methodology, and statistics. Investigators will have to be trained with a prespecified standard operating procedure before the trial, including eligibility criteria, interventions, details in filling eCRF, assessment of outcomes, and data management. An inspection plan will be designed for quality control, and professionals will be hired to supervise the research process. Moreover, patients will be allowed to use authorized accounts in WeChat to fill out the eCRF to improve compliance. The system will send reminders to patients to fill out the eCRF. In addition, the research assistants and clinical research coordinators will be able to monitor participants’ research records through the researcher management backstage.

### Sample size calculation

The study’s treatment duration will be 8 weeks, with the responder rate of the clinical symptoms of FD-PDS after 8 weeks of treatment being the primary efficacy endpoint. To control the overall false-positive error in the trial and to ensure the power of the test, the study will adopt the following assumptions: alpha level of 0.05 (2-sided) and power of 0.8, with the ratio of the number of cases in the ZZKZ group and the placebo group as 1:1. According to the results of a multicenter clinical study of ZZKZ completed by [name] in the First Affiliated Hospital of Sun Yat-sen University, with the cooperation of 16 domestic hospitals, the responder rate for clinical symptoms of FD-PDS has been set 54% with the ZZKZ and 38% for the placebo [16]. Calculation of sample size indicates that 187 cases will be required in the ZZKZ and placebo groups respectively. Assuming a dropout rate of 20%, a total of 480 cases will be required for our study.

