### Statistical analysis

Statistical analysis will be performed using SAS 9.3 software by an independent statistician. All statistical tests will use a two-sided test, *P* ≤ 0.05 will be regarded as significant. A 95% confidence interval will be used. Based on the intention-to-treat principle, the missing data will be replaced by the last data (i.e., the missing efficacy data will be replaced by the efficacy data of the previous follow-up). The efficacy analysis will be mainly based on a full analysis set, and the central effect will be considered. The primary efficacy endpoint will be tested for superiority. The efficacy between groups will be compared using the Cochran-Mantel-Haenszel-*χ*^2^ test with and without regard to center stratification, and a 95% confidence interval of the difference between groups will be calculated. Method repetitive measure analysis of variance will be used to analyze the secondary outcome of VAS scores at different time points between groups. Sub-analysis will be carried out to review whether there is a difference in the effect of ZZKZ according to demographical data across countries. The safety analysis will be mainly based on descriptive statistics. The adverse events that occur in this trial will be described in a list, and the incidences will be compared using Fisher’s exact probability test.

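### The stated 187 per arm does not follow from the stated inputs: these need 149 to 164 per arm, and 187 gives about 88% power rather than 80%

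*Protocol article*

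**What the plan says.** All inputs are in one paragraph of the protocol article, under Sample size calculation. The error rates are "alpha level of 0.05 (2-sided) and power of 0.8". Allocation is equal: "with the ratio of the number of cases in the ZZKZ group and the placebo group as 1:1". The planning rates are explicit: "the responder rate for clinical symptoms of FD-PDS has been set 54% with the ZZKZ and 38% for the placebo". The result follows: "Calculation of sample size indicates that 187 cases will be required in the ZZKZ and placebo groups respectively". The last sentence adds the allowance for losses: "Assuming a dropout rate of 20%, a total of 480 cases will be required for our study".

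Under Statistical analysis the hypothesis is plain superiority: "The primary efficacy endpoint will be tested for superiority". The comparison is a Cochran-Mantel-Haenszel chi-square "test with and without regard to center stratification, and a 95% confidence interval of the difference between groups will be calculated". Neither section mentions a margin, a split of alpha, a design effect or any other factor that would raise the required number.

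**The concern.** The article does not leave the calculation to another document. It gives a full set of inputs and an output, and the output is well above what those inputs produce. Either 187 is wrong, or at least one stated input or the implied formula is not the one used.

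What is at stake is the reported design, not the validity of the test. The required number and its power will probably be repeated in the trial report. A reader would take 187 evaluable per arm as the threshold for 80% power, when about 152 reach it. A reader judging a null result would credit the design with 80% power when its own assumptions give more. The justification for enrolling 480 also cannot be reproduced from what is printed.

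**Working it through.** **Inputs**, all from Sample size calculation: p1 = 0.54, p2 = 0.38, difference d = 0.16, mean rate 0.46, z for two-sided 0.05 = 1.960, z for power 0.80 = 0.8416, allocation 1:1, dropout 20%.

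**Step 1. Try to reproduce 187.**

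- Pooled variance (uncorrected chi-square): n = [1.960·√(2·0.46·0.54) + 0.8416·√(0.54·0.46 + 0.38·0.62)]² / 0.16² = (1.3815 + 0.5855)² / 0.0256 = 151.1, so **152**.
- Unpooled variance: n = (0.2484 + 0.2356)·(1.960 + 0.8416)² / 0.0256 = 148.4, so **149**.
- Arcsine: 150.98, so **151**.
- Continuity-corrected: n = (151.1/4)·[1 + √(1 + 4/(151.1·0.16))]² = 163.4, so **164**.
- Exact Fisher test: power is 0.799 at 162 and 0.808 at 164 per arm, so about **162 to 164**.
- One-sided alpha would lower the number (119, or 132 with continuity correction).

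None gives 187. It is 23% above 152 (187/152 = 1.23) and 14% above 164 (187/164 = 1.14), too much for rounding or choice of formula.

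**Step 2. Power under the stated rates.** Power = Φ{[0.16·√n − 1.3815] / 0.6957}.

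| Per arm | Where it comes from | Power, uncorrected | Power, continuity-corrected |
|---|---|---|---|
| 152 | required by the stated inputs | 0.802 | – |
| 187 | stated in the protocol | 0.877 | about 0.85 |
| 192 | 480 less 20%, halved | 0.885 | about 0.86 |
| 240 | all randomised | 0.943 | about 0.93 |

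For 187: (0.16·13.675 − 1.3815)/0.6957 = 1.159, and Φ(1.159) = 0.877.

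**Step 3. The dropout step.** 187/0.8 = 233.75, so 234 per arm and 468 in total. The stated 480 is 2.6% higher (480/468 = 1.026), an ordinary round-up to 240 per arm.

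**Step 4. Where 187 might come from.**

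- 149/0.8 = 186.25, rounded up to 187. This matches if the unpooled figure is rounded before inflation; without that rounding, 148.39/0.8 = 185.5, so 186. From the pooled figure, 152/0.8 = 190.
- Inputs the document does not state also come close: power 0.85 with continuity correction gives 185, and two-sided alpha 0.025 gives 184.

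**Step 5. Total with one 20% inflation.** 152/0.8 = 190 per arm, 380 in total. Across formulas the total runs from 374 (149/0.8, so 187 per arm) to 410 (164/0.8 = 205 per arm). The stated 480 is 70 to 106 above that range.

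**The case against.** The strongest reply is that the discrepancy does no inferential harm. It errs towards more patients; type I error, the primary test and the estimate are untouched; no decision rule is tied to 187; and the finished trial will be judged mainly by the confidence interval that the protocol specifies. This stands, and it limits the seriousness of the point. It does not make the printed figure right.

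Two stronger readings are tempting, and the documents support neither.

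- A reader might infer that dropout was counted twice. The match of 149/0.8 to 187 is suggestive, because the next sentence applies the same 20%. But it depends on one formula and one order of rounding, other unstated inputs come within a few patients, and the protocol does not say how 187 was obtained. It remains one possible explanation.
- A reader might add that 480 is a second error, since 374 of 480 implies 22% loss (1 − 374/480 = 22.1%). That only restates the rounding from 468 to 480.

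A further fair point concerns the benchmark. Efficacy is to be analysed mainly in the full analysis set with the last value carried forward, so patients who drop out after giving data may stay in the analysis. A correction that quoted only 192 per arm would then understate the number analysed. This stands and is reflected in the fix.

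**Conclusion.** The stated 187 per arm is not the result of the stated inputs. They give 149 to 164 per arm, and 152 for the uncorrected chi-square test. Under the stated rates 187 gives about 88% power (about 85% with continuity correction), not 80%. The break lies between the inputs and 187; the later step to 480 is acceptable.

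The error is conservative. It should be fixed, but it does not threaten the trial's conclusions. The finding assumes only the printed inputs and a standard two-proportion comparison with no margin or design effect, since none is stated. The power figures hold if the true rates are 54% and 38%, and they ignore centre stratification, for which the protocol gives no planning values.

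**What to change.** Restate the paragraph and leave enrolment at 480. Suggested content: with 54% versus 38%, two-sided alpha 0.05 and 1:1 allocation, about 152 evaluable patients per arm give 80% power (164 with continuity correction). The 480 randomised give about 88% power if 20% are lost from the analysis (192 per arm), and up to about 94% if all 240 per arm are in the full analysis set.

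If 187 came from other rates, another power, another alpha or another formula, state those inputs instead so that the figure reproduces. In either case, apply the dropout inflation once and say which number it is applied to.

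The cost is a wording correction in the protocol, carried into any other trial document that repeats the figure. Recruitment, randomisation and the analysis are unaffected.
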